**Aim 1: Estimate the post-tax changes in SSB intake after implementation of the South African SSB tax policy.**

**Data and Subjects**

We will analyze 24-hour dietary recalls and beverage-related FFQ data from the Langa 18-39y Survey of young township adults (n=2383) from Cape Town, South Africa. We will estimate beverage intake at baseline, 6 months, and 12 months of data collection, with beverages categorized as taxed/untaxed according to the 4g of sugar per 100ml threshold.

**Outcomes**

Our primary outcomes are taxed beverage volume, taxed beverage calories, untaxed beverage volume, and untaxed beverage calories. Secondary outcomes will include volume and calories of taxed and untaxed beverage sub-categories (Table 3), as well as total beverages.

**Analysis Plan**

*Adjusted estimates of overall taxed and untaxed beverages*

Our first objective will be to perform a descriptive/unadjusted analysis, examining the mean and distribution (intakes for top and bottom quintiles) of taxed and untaxed beverage categories and subcategories (Table 3) at each time point, as well as the percentage of our sample that reported consuming beverages in that category.

Our next objective will be to examine the mean adjusted volume and calories per capita and per consumer at baseline, 6 months, and 12 months after the SSB tax was implemented for overall taxed and untaxed beverages. We will perform this analysis using two different approaches with respect to the FCT linkage used. For the first approach, we will analyze beverage intakes using the February/March 2018 UNC-UWC Food Composition Table linked to baseline, 6 month, and 12 month data. Pre-post beverage intake comparisons will be made using this same FCT across all three time points. As a result, changes in mean taxed SSB intake will reflect **behavioral changes only**, since we effectively assume no reformulation by keeping the same FCT. In other words, the only way taxed beverages can decrease is for consumers to consume less (as opposed to beverages shifting from being taxed to untaxed due to reformulation).

For the second approach, to account for possible effects of reformulation and the fact that the nutrient composition of the beverages may be changing over time, we will use our 2018 FCT for baseline data and then link the updated February/March 2019 FCT to the dietary intake data for 12 months. In this approach, changes in the mean volume of taxed beverage intake could be driven by changes in behavior or **changes in taxed beverage classification** (if beverages switch from one side of 4g/100ml threshold to the other). In addition to these reasons, changes in the mean calories of taxed beverages could be due to **changes to within-beverage category sugar concentration** (e.g. taxed beverages remain taxed but reduce their caloric content). We will not repeat the analysis for 6 month data because updated nutrition information was not collected at 6 months.

Linear regression models will be used to estimate taxed and untaxed beverage consumption at each time point, adjusted for the covariates listed in Table 4. We will estimate unadjusted results, adjusted results (including individual level-covariates, weekday of intake, and temperature), and finally results adjusted for these covariates plus BMI. These models will include adjustment for total energy when using 24-h recall data. Given that our FFQ cannot be used to obtain total energy intake, adjusting for BMI will allow us to potentially control for variation in total energy intake in our sample. Comparisons between baseline and 6 month and between baseline and 12 month means will be made with two-tailed t tests. We plan to use both the 24-h recall and the FFQ for these analyses. For the FFQ, we will multiply the amount reported as most commonly consumed times a frequency per day (e.g. intake amount of once per week would be multiplied by 1/7) to obtain daily intake.

**Table 4. Outcomes and Covariate measures for model adjustment**

| **Primary outcomes** |  |
| --- | --- |
| Taxed beverage volume | Taxed based on having more than 4g of sugar per 100ml |
| Taxed beverage calories |  |
| **Secondary outcomes** |  |
| Untaxed beverage volume | Untaxed based on having less than 4g of sugar per 100ml |
| Untaxed beverage calories |  |
| **Potential modifiers** |  |
| SSB knowledge | Latent variable obtained from confirmatory factor analysis (CFA), for knowledge of whether selected beverages contain added sugars. |
| SSB risk perception | Latent variable obtained from confirmatory factor analysis (CFA), for perceived risk of NCDs due to SSB consumption |
| **Covariates** |  |
| Individual-level covariates | Age (continuous, range 18-39), sex, total energy intake, BMI, smoking (yes/no), alcohol intake, socioeconomic status (ordinal categorical), disease status (diagnosis of diabetes, heart disease, high cholesterol, high blood pressure, cancer, or obesity) |
| Weekday | Diet intake reported for weekday versus weekend (binary) |
| Temperature | Obtained from South African Weather Service, to control for seasonal changes in SSB intake |
| Time period | Categorical: 0 (baseline), 1 (6 months), 2 (12 months) |

**Expected Results:** Based on results from Mexico and Chile where an SSB tax was implemented, we hypothesize that taxed SSB consumption by 18-39 year-olds living in Langa will decrease by 6% at 12 months. Based on the magnitude of change reported from previous SSB tax evaluations, we do not expect to have sufficient power to detect a statistically significant change in taxed SSB consumption by 6 months.

*Analysis of taxed/untaxed beverage subcategories*

We will repeat the above analysis for beverage subcategories (Table 3), using both approaches for linking FCT data to dietary intake data to account for potential reformulation across beverage subcategories.

*Comparison of diet assessment methods*

Our study utilizes two different methods of diet assessment, one 24-h recall and one FFQ, to measure beverage intake in our Langa population. We will perform separate analyses using data from the **24h recall** and **beverage frequency questionnaires** to estimate intakes of our key outcome variables including total beverage calories, taxable beverage calories, untaxable beverage calories, and total sugar content. We will then compare agreement between the change in mean intakes of these key outcome variables from baseline to 6 months and from baseline to 12 months for the two sources of dietary intake data. We will calculate correlation coefficients to statistically compare agreement depending on the outcome of a Shapiro-Wilk test for normality of the nutrients under consideration. If the distributions are normal, then we will use Pearson correlation coefficients. If the distributions are non-normal, then we will use the nonparametric Spearman correlation coefficients^78,79^.

Using both the 24h recalls and FFQ will provide a more complete picture of change in beverage intake, as there are different strengths and weaknesses of each dietary assessment method. Compared to food frequency questionnaires, 24h hour recalls are a more accurate measure of dietary intake, but are subject to greater within-person variation. Because this within-person variation in day to day intake is due to random error, the mean random error is expected to be zero over a population if the administration of the recall is collected across days of the week^44^. Therefore, a single administration of a 24-hour recall on the entire sample at both time points is a suitable and sufficient method for performing a pre-post intervention assessment of mean dietary intake^44^. Thus, our main outcome will be beverage intake as measured by the 24-h recall.

However, one key limitation of using 24-h recalls for capturing dietary intake is that they **may not capture episodic consumption of some beverage categories** and are subject to greater variance when only one recall is used^80,81^. In this study, because overall consumption of SSBs is high (>90% consumers), this is less of a concern for overall SSBs than it is for beverage sub-categories, which may be more likely to be episodically consumed. To address this concern, usual intake methods such as the NCI method^82,83^ or MSM^84–86^ have been developed; however, these methods require at least two 24-h recalls in a subsample of the target population, which we do not have. Therefore, instead of using usual intake methods, we plan to address this issue by using both the 24h recall and an FFQ to examine pre-post population mean intakes. Using the FFQ to examine pre-post means is advantageous because it covers a longer time period than the 24h recall and thus better reflects usual consumption.

In addition, FFQs can be used to supplement 24-h recall data to distinguish true nonconsumers from occasional nonconsumers^85^. We will examine how well the 24-h recall captures consumers compared to the FFQ by first identifying those who report any consumption of a beverage category according to the FFQ. We will then determine what percentage of true consumers are also identified as a consumer in the 24h recall.

Using regression models with a high number of non-consumers (zero value for consumption) can bias results. For beverage categories with <90% consumers, we will estimate beverage intake from 24-h recalls using a two-part model. The basic structure of the two part model is: *Total amount of beverage category consumed = [Probability to consume beverage category] * [Amount of beverage category if consumed]*. First, the two-part model uses a logistic regression model for the binary choice of the probability to consume the beverage. Second, conditional on a positive outcome, an OLS regression model with log-transformed y in the second part is used to model the beverage consumption^87^. Standard errors and confidence intervals are calculated for retransformed values using a nonparametric bootstrap from the Stata **margins** command^87^. Models are adjusted for the same covariates in both steps.

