**Limitations**

*Study design*

Given that our data are cross-sectional and not longitudinal, we are not able to follow individuals over time, only measure differences in population means. Social desirability bias could affect reporting of SSB intake and cause us to underestimate SSB intake. It is also possible that after the tax, social norms may have shifted so that the effect of social desirability bias is even greater after SSBs are subject to tax, causing an overestimation of reductions in SSB intake in this population.

*Repeated individuals across data collection periods*

We are using a repeated cross-sectional study design, and it is possible that we have repeated individuals surveyed at more than one time point. We do have a variable that indicates whether participants were included in our sample at previous data collection points, but the individual identifiers were generated using a method that does not allow for individuals to be linked across time. This limitation could potentially bias our results by an unknown magnitude and direction, given that we cannot know whether repeated individuals were high or low consumers of a given beverage category.

*Accuracy of FCT beverage codes*

Although the beverage codes that we are developing for our UNC-UWC FCT are based on nutrition information of South African beverages, they still represent an average and therefore it is possible that some beverages may be misclassified as taxed or untaxed if the actual products consumed differ in their sugar content to the average sugar content calculated for the beverage category. For example, if there is brand-specific reformulation, where some soda brands reduce their sugar (to become untaxed) and others do not (remain taxed), this could lead to misclassification. The potential for misclassification of beverages is even greater for the FFQ versus the 24-h recall because the beverage categories reported are broader than the individual beverage codes contained within each beverage subcategory.

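### Correlations between the 24-h recall and the FFQ cannot show whether the two instruments agree on the change in mean intake

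*Protocol*

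**What the plan says.** The section Comparison of diet assessment methods (Aim 1) starts from the fact that each participant gives one recall and one FFQ: "Our study utilizes two different methods of diet assessment, one 24-h recall and one FFQ, to measure beverage intake in our Langa population". Separate analyses by instrument are planned. The target of the comparison follows: "We will then compare agreement between the change in mean intakes of these key outcome variables", for baseline to 6 months and baseline to 12 months. The outcomes named are calories from total, taxable and untaxable beverages, and total sugar.

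The next sentence gives the statistic: "We will calculate correlation coefficients to statistically compare agreement depending on the outcome of a Shapiro-Wilk test for normality of the nutrients under consideration". The rule for choosing the coefficient is "If the distributions are normal, then we will use Pearson correlation coefficients" and "If the distributions are non-normal, then we will use the nonparametric Spearman correlation coefficients".

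The Aim 1 Limitations describe the design: "Given that our data are cross-sectional and not longitudinal, we are not able to follow individuals over time, only measure differences in population means". For people who happen to be surveyed more than once, "the individual identifiers were generated using a method that does not allow for individuals to be linked across time".

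**The concern.** The quantity to be compared and the statistic named for it do not fit together. The target is a pair of changes in means, one per instrument. A correlation needs many pairs of values, and with unlinked waves no participant has a change score on either instrument. The only participant-level correlation available is between recall and FFQ levels inside one wave, and that answers a different question.

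Two misreadings could follow. A respectable within-wave correlation could be written up as agreement in change when the instruments in fact moved differently. Conversely, a weak correlation could be written up as disagreement when both means moved alike. The protocol itself explains why the second can happen: it says a single recall carries random day-to-day error that averages out over the population. Such error leaves the mean intact but pulls the person-level correlation down.

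The FFQ is brought in to support the pre-post comparison of means where one recall is weak, chiefly for beverages drunk only occasionally. Readers will therefore want to know whether the two instruments tell the same story about change.

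**Working it through.** The protocol states no figure on this point, so there is none to reproduce. The check is logical, with illustrations.

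**1. What can be computed.** For one outcome and one contrast, each instrument yields a single number:

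- recall change = mean recall (follow-up) − mean recall (baseline)
- FFQ change = mean FFQ (follow-up) − mean FFQ (baseline)

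That is one pair, and no correlation can be formed from one pair. Pooling the named outcomes would give only four pairs per contrast, and they overlap because total calories contain the taxable and untaxable parts. Within a wave, by contrast, everyone has both instruments, so correlations of levels can be computed.

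**2. Whether a within-wave correlation reflects agreement in change.** Multiply every follow-up recall value by a positive constant c. The mean recall moves by the factor c, but ranks are unchanged, so Spearman is identical. Pearson is also unchanged by positive rescaling. The change in the recall mean can therefore take any proportional value with no effect on either coefficient.

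Illustration. Inputs: baseline FFQ total SSB mean 1054 and SD 1071 ml/day (Table 1). Assumptions not in the documents: gamma-shaped intake, the same mean and SD for the recall, a latent correlation of 0.4 between instruments, and 200,000 simulated people per wave. A 6% change is 0.06 × 1054 = 63 ml/day, giving follow-up means of 991 or 1117.

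| Scenario | Spearman, baseline / follow-up | Pearson, baseline / follow-up | Simulated change, FFQ / recall (ml/day) |
|---|---|---|---|
| Both fall 6% | 0.385 / 0.385 | 0.353 / 0.351 | −61 / −65 |
| FFQ falls 6%, recall rises 6% | 0.388 / 0.381 | 0.355 / 0.353 | −68 / +61 |

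The intended difference in change is 0 in the first row and 63 − (−63) = 126 ml/day in the second. The coefficients do not separate the two; their small differences are simulation noise.

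**3. Bias in level.** Let FFQ = 2 × recall for everyone. Pearson and Spearman are both 1.00. The mean difference is about 1050 ml/day, and Lin's concordance is 4 × 1071² / (5 × 1071² + 1054²) = 4,588,164 / 6,846,121 = 0.67.

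**4. What a direct contrast could deliver.** Let D be recall minus FFQ in one person. Recall change minus FFQ change equals mean D at follow-up minus mean D at baseline. With SD 1071 for both instruments and Pearson 0.353, Var(D) = 2 × 1071² × (1 − 0.353) = 1,484,271, so SD(D) = 1218. Assume 2,383 people in each wave (the protocol gives this for baseline only) and independent waves. Then SE = 1218 × √(2/2383) = 35.3, and the 95% half-width is 1.96 × 35.3 = 69 ml/day. For correlations from 0.2 to 0.6 the half-width runs from 77 to 54. Treating a person's two instruments as independent gives SD 1515, SE 43.9 and half-width 86, so the pairing matters. Volume stands in here for the calorie and sugar outcomes, for which the protocol gives no SD.

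**5. The normality test.** With 2,383 people, Shapiro-Wilk at 0.05 rejected in 100% of 300 runs for gamma data with the Table 1 mean and SD, in 100% at skewness 0.3 and in about 96% at skewness 0.2. The rule will almost certainly end at Spearman.

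**The case against.** The strongest reply is that the protocol does not hide a conflict between instruments. The Aim 1 Analysis Plan tests baseline against 6 and 12 months for both the recall and the FFQ, and the comparison section repeats that the analyses are separate. If one instrument fell and the other did not, both results would be on the page. The recall is also named as the main outcome, and no decision rule uses the correlation. All of this stands. It confines the fault to the comparison step, but it does not give that step a statistic that answers its question.

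A second reply is that testing normality of nutrient distributions points to participant-level intakes, so the authors probably mean within-wave correlations. That is a fair reading. A reader might infer that the planned analysis is impossible; the documents do not support that, because each person completed both instruments within a wave. Only a correlation of changes is unavailable. The within-wave version is a legitimate measure of relative ranking, but the protocol presents it as evidence on agreement in change.

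A reader might also take the Shapiro-Wilk step as a fault that affects results. It does not. The step leads to the coefficient that would be kept anyway, so it deserves only a remark.

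Finally, it could be said that such detail belongs in a statistical analysis plan. Here, however, the protocol itself fixes the target, the statistic and the selection rule, and the statistic does not address the target.

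**Conclusion.** The point holds in a limited form. Pearson or Spearman coefficients, which here can only be within-wave correlations of levels, cannot support a statement that the recall and the FFQ agree on the change in mean intake. They came out practically the same when the true changes were equal and when they differed by 126 ml/day in opposite directions. The exact values rest on the assumed gamma shape, the Table 1 FFQ moments applied to both instruments, and a latent correlation of 0.4. The invariance behind them holds for any proportional change and needs none of these assumptions.

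It would be wrong to infer that the main finding of Aim 1 is at risk. That estimate comes from the recall alone, and each instrument's own change will still be reported. This is a secondary method comparison that should be corrected.

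**What to change.** For each outcome and each contrast (6 months and 12 months against baseline), report recall change minus FFQ change, or the equivalent instrument-by-time term, with a confidence interval. Keep both instruments of one person together, for example by a bootstrap that resamples persons within wave.

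Use unadjusted estimates or the same covariate set for both instruments. The Analysis Plan adjusts the recall models for total energy and says the FFQ cannot supply it, so a contrast of the adjusted results as planned would mix instrument with adjustment.

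Interpret the interval, not just its p-value. On the assumptions above its half-width is of the same order as a 6% change (69 against 63 ml/day), so an interval that includes zero would not by itself establish agreement.

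Name Spearman in advance, drop the normality test as a selector, and label the coefficient as within-wave ranking of individuals. Limits of agreement between a one-day recall and a past-month FFQ are optional and not needed here.

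The cost is a few sentences of protocol text and a short bootstrap or clustered model, with no new data.

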**Limitations**

*Study design*

Given that our data are cross-sectional and not longitudinal, we are not able to follow individuals over time, only measure differences in population means. Social desirability bias could affect reporting of SSB intake and cause us to underestimate SSB intake. It is also possible that after the tax, social norms may have shifted so that the effect of social desirability bias is even greater after SSBs are subject to tax, causing an overestimation of reductions in SSB intake in this population.

*Repeated individuals across data collection periods*

We are using a repeated cross-sectional study design, and it is possible that we have repeated individuals surveyed at more than one time point. We do have a variable that indicates whether participants were included in our sample at previous data collection points, but the individual identifiers were generated using a method that does not allow for individuals to be linked across time. This limitation could potentially bias our results by an unknown magnitude and direction, given that we cannot know whether repeated individuals were high or low consumers of a given beverage category.

*Accuracy of FCT beverage codes*

Although the beverage codes that we are developing for our UNC-UWC FCT are based on nutrition information of South African beverages, they still represent an average and therefore it is possible that some beverages may be misclassified as taxed or untaxed if the actual products consumed differ in their sugar content to the average sugar content calculated for the beverage category. For example, if there is brand-specific reformulation, where some soda brands reduce their sugar (to become untaxed) and others do not (remain taxed), this could lead to misclassification. The potential for misclassification of beverages is even greater for the FFQ versus the 24-h recall because the beverage categories reported are broader than the individual beverage codes contained within each beverage subcategory.

**Aim 2:** **Examine changes in tax awareness, SSB knowledge, and SSB risk perception, and determine whether these variables modify the relationship between SSB consumption and time since tax implementation.** The key goal for Aim 2 is to test whether tax awareness, knowledge, or risk perception change over time after tax implementation and whether these variables modify the relationship between SSB consumption and time since tax implementation. We will test (1) whether there are significant differences in mean SSB knowledge, risk perception and prevalence of tax awareness before and after the tax (2) whether there is a time*modifier interaction on taxed SSB intake, pooling data from baseline, 6, and 12 months. Aim 2 will be completed using the same study population as Aim 1. The rationale for this analysis is depicted in Figure 4, where SSB knowledge score modifies the relationship between SSB tax implementation and SSB consumption.

